5.14 STATISTICS

Primary endpoint is PWV (brachial) and PWV (aortic) with a minimum clinically relevant difference of 1 m/s. Based on previous reproducibility (29) the standard deviation is 1.1 and 0.75 m/s for brachial and aortic PWV, respectively. The power of the t-test by comparing the two distributions is at n = 20 at 0.82 and 0.99 for brachial and aortic PWV, respectively.

A P-value less than 0.05 is considered significant.
Data from discontinued subjects can be assessed for each completed treatment period. Withdrawn participants are replaced by new subjects, so the size of patient population is achieved.
A professional statistician is associated with the project and has advised in creating the design. Data processing will be conducted under the guidance of the very same professional statistician.

**6. Quality control and quality assurance**General procedures for quality control and quality assurance will be followed in accordance with the ICH GCP Guidelines. Data will be monitored by the University GCP unit. In connection with the informed consent a permission is obtained from the study participants, that the research ethics committee, the Medicines Agency and the GCP unit can access information about their health. A copy of the proposed text is attached as Annex IIIa.

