**5. Description of project**

5.1 PURPOSE

To assess the effect of dual blockade of renin-angiotensin system with ACE inhibitors (ACE-I) and angiotensin II antagonists (AIIA) on pulse-wave morphology and pulse-wave velocity (PWV) in patients with chronic renal failure assessed with the applanationtonometry method. Furthermore, a comparison of the effect of single blockade respectively ACE-I and AIIA is wanted.
The hypothesis is that dual blockade of renin-angiotensin system leads to a greater reduction of arterial stiffness than single therapy alone. We expect no difference in treatment effect between ACE-I and AIIA.

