5.5 DESIGN

Open randomized crossover trial in patients with non-dialysis chronic renal failure study:

• The effect of treatment with either ACE-I or AIIA on parameters of arterial stiffness assessed by the applanationtonometry method.
• The effect of treatment with both ACE-I and AIIA on parameters of arterial stiffness assessed by the applanationtonometry method.

The patient population is divided into 2 groups: one group with prior treatment with either ACE-I or AIIA (group I) and another group without prior treatment with either ACE-I or AIIA (group II). The study medication is as follows: the ACE inhibitor Enalapril and angiotensin receptor antagonist Candesartan. The study extends over three periods of 8 weeks. Patients in group I are randomized to receive either Enalapril in both the first and second periods or Candesartan in both the first and second periods. Patients in group II is randomized to either treatment with Enalapril or candesartan in the first period with a shift to the opposite drug in the second period.
Common to both groups is a double treatment with both Enalaprilat and Candesartan in the third period.
There will be carried out measurements at baseline and after the first, second and third period. Each study includes measurement by the applanationtonometry method where the tonometry is placed with gentle pressure towards the skin above the radial artery , thereby providing data for pulse wave analysis. Subsequently, measurements are performed equivalent to the radial, carotid and femoral arteries, thereby providing data for pulse wave velocity determination. The study design is shown in flow diagrams attached as Annex Ia + b.
There must be delivered 24 h urine collection before baseline and after every period. Chromium-EDTA clearance is carried out before and at the last visit in the trial.

*Patients receiving ACE-I or AIIA therapy prior to the trial.*
Pulse wave measurements are carried out at baseline and after each treatment period of 8 weeks, a total of 4 times. In addition comes 6 clinical control sessions and two appearances for the making of Chromium-EDTA clearance before and after the project.

Measurement I (start)

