5.12 PRACTICAL PERFORMANCE

Patients who are interested in participating in the study are informed about the project. The written patient information (Annex IA, IB and III) obtained and reviewed and a possibly. consent is issued.

A time schedule is agreed for Chromium-EDTA clearance, the measurements and the clinical controls.

Demographic data is recorded, possibly using the patient record.

*Randomization*Prior treatment with ACE-I/AIIA: Randomization is done by drawing lots from a bag in which there are 40 notes. Half of these are inflicted ACE-I treatment and the other half is applied AIIA therapy. Randomization for the group of patients without prior ACE-I/AIIA is done in the same way by lot from a bag, half of the 20 notes bearing the ACE-I in the first period and AIIA in the second period and the other half is applied AIIA in the first period, and ACE-I in the second period. The result of the randomization is recorded in the patient's Case Report Form.

*Measurement I-VI*The day before the measurements the patient collects urine in a dunk.
At the day of the first measurement the patient does not take his usual medications until after the measurement. In case of diabetes, the habitual diabetes medication is taken as usual, but all other medications are taken after the measurement. At the other measurements the study medication is taken 2 hours before meeting time, but all other medications taken after the measurement, except from antidiabetic medication. On arrival the patient is weighed. The patient brings 24 h urine collection.

At study start (baseline) blood sampling is taken in a peripheral vein for analysis of: b-hemoglobin, b-leukocytes, b-platelets, p-bilirubin, p-ALT, p-alkaline phosphatase, hsC-reactive protein, p-creatinine , p-urea, p-sodium, p-potassium, p-bicarbonate, glucose, p-albumin, p-cholesterol, p-triglyceride, p-urate, p-parathyroid hormone and p-homocysteine.

At the other measurements and clinical controls the following blood samples are taken for analysis: b-hemoglobin, p-creatinine, p-urea, p-albumin, p-potassium and p-sodium.

The patient is placed supine on a bed in a quiet room and is resting for 15 minutes. A blood pressure is recorded by a mercury sphygmomanometer.

Data is recorded in the schedules attached as Annex IIA and IIB.

*Clinical controls*

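### If the t-test named in the power statement is carried into the analysis, the between-patient enalapril-versus-candesartan comparison of PWV makes poor use, or no use, of the baseline PWV collected on every patient

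*Protocol*

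**What the plan says.** Protocol section 5.14 makes brachial and aortic PWV the primary endpoint, with a "minimum clinically relevant difference of 1 m/s". It attributes the planning SDs to an earlier reproducibility study: "the standard deviation is 1.1 and 0.75 m/s for brachial and aortic PWV, respectively". It then gives the power: "The power of the t-test by comparing the two distributions is at n = 20 at 0.82 and 0.99 for brachial and aortic PWV". The significance rule is "A P-value less than 0.05 is considered significant". No other test or model for PWV appears, and section 5.14 mentions neither a baseline covariate nor the prior-treatment group. It leaves data processing to the guidance of the project statistician.

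Three other places bear on this:

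- Section 5.5: "There will be carried out measurements at baseline and after the first, second and third period". Every patient therefore has a PWV value before the randomised drug starts. In group I (prior ACE-I or AIIA) each patient stays on one single drug through periods 1 and 2. In group II (no prior treatment) patients cross over between the two drugs.
- Section 5.12: group I is drawn from a bag of 40 notes, half for each drug. For the other group, "Randomization for the group of patients without prior ACE-I/AIIA is done in the same way by lot from a bag", here with 20 notes.
- Section 5.1: the hypothesis concerns dual against single blockade. The two single drugs come second: "Furthermore, a comparison of the effect of single blockade respectively ACE-I and AIIA is wanted". No difference between them is expected.

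**The concern.** In group I no patient receives both drugs as monotherapy within the trial, so enalapril versus candesartan is a comparison between patients. Patients differ persistently in PWV, and a t-test of on-treatment values leaves that spread in the error term. Any chance difference in baseline PWV between arms of 20 then passes straight into the estimate. A t-test of change from baseline uses the baseline, but fixes its coefficient at 1. That is less efficient than estimating the coefficient, except when the correlation is very high.

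The protocol already collects the baseline value. What is at stake is the precision of the single-drug comparison. This matters because the investigators expect no difference there, and a finding of no difference is only as informative as its confidence interval is narrow.

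**Working it through.** **Inputs.** From section 5.14: difference 1 m/s; SD 1.1 (brachial) and 0.75 (aortic); n = 20; alpha 0.05, taken as two-sided because that reproduces the stated power. From section 5.12: 20 versus 20 in group I. The protocol gives neither the baseline-to-follow-up correlation (rho) nor the total between-patient SD (T), so both are assumed and varied. The SD is taken as equal at baseline and on treatment. The small variance inflation from chance baseline imbalance is ignored.

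**Step 1: the plan's own figures.** Normal approximation, 20 per arm: power = Φ(1 / (SD × √(2/20)) − 1.96).

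- Brachial: 1 / (1.1 × 0.3162) = 2.875; Φ(0.915) = 0.82.
- Aortic: 1 / (0.75 × 0.3162) = 4.216; Φ(2.256) = 0.99.

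Both match. A paired test with n = 20 and the stated SD as the SD of differences gives 0.97 and 1.00, which does not match. The exact noncentral-t values for the unpaired test (38 degrees of freedom) are 0.80 and 0.98; they are the reference below.

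**Step 2: baseline as covariate, stated SDs read as between-patient SDs.** Residual SD = SD × √(1 − rho²), 37 degrees of freedom. The change-score SD is SD × √(2(1 − rho)).

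| rho (assumed) | Residual SD, brachial | Raw t-test | Change-score t-test | Baseline-adjusted |
|---|---|---|---|---|
| 0.3 | 1.05 | 0.80 | 0.66 | 0.84 |
| 0.5 | 0.95 | 0.80 | 0.80 | 0.90 |
| 0.7 | 0.79 | 0.80 | 0.95 | 0.98 |

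For aortic PWV the raw test has 0.98 and the adjusted model 0.99 or more at each rho, so there is no material gain.

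**Step 3: stated SDs read as SDs of change.** Here rho = 1 − SD²/(2T²), and the residual SD is T × √(1 − rho²). The change-score t-test has 0.80 (brachial) and 0.984 (aortic).

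- Brachial, T = 1.5: rho = 1 − 1.21/4.5 = 0.731, residual SD 1.02, adjusted power 0.85.
- Brachial, T = 3: rho = 1 − 1.21/18 = 0.933, residual SD 1.08, adjusted power 0.81.
- Aortic, T = 1.5 to 3: adjusted power 0.989 to 0.985.

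The gain is about 1 to 5 points for brachial PWV and under 1 point for aortic PWV.

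**Step 4: stated SDs read as within-patient SDs.** Here rho = 1 − SD²/T², and the change-score SD is SD × √2 (1.56 brachial, 1.06 aortic).

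| T (assumed, m/s) | Raw t-test, either site | Brachial: change / adjusted | Aortic: change / adjusted |
|---|---|---|---|
| 1.5 | 0.54 | 0.51 / 0.64 | 0.83 / 0.87 |
| 2 | 0.34 | 0.51 / 0.58 | 0.83 / 0.85 |
| 2.5 | 0.23 | 0.51 / 0.55 | 0.83 / 0.84 |
| 3 | 0.18 | 0.51 / 0.54 | 0.83 / 0.84 |

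Against the change-score test the gain is about 3 to 13 points (brachial) and 1 to 5 points (aortic). Against the raw test it is 10 to 36 points (brachial) and 34 to 66 points (aortic).

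**Step 5: the randomisation groups.** n = 20 per arm fits group I alone, which is one bag and so one randomisation stratum. A group term is needed only if groups I and II are pooled, for example at the end of period 1, when 20 + 10 = 30 patients are on each drug.

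**The case against.** The strongest answer is that the protocol never declares the t-test to be the analysis. It appears only in the power sentence, and model and covariates are commonly left to a statistical analysis plan, which is not at hand here. A simple test used for sizing does not bar an adjusted analysis. This stands, and it is why the point is conditional.

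A reader might infer that the plan ignores the baseline. The text does not support that: it does not say whether the two distributions are raw values or changes, and the hypothesis in 5.1 is worded as a reduction. A t-test on changes with SD 1.1 and 20 per arm gives the same power figure.

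A reader might also infer a failure to respect separately randomised groups. On the natural reading the test lies within group I, so no stratum is ignored. Patients with prior ACE-I and prior AIIA share one bag and are not randomised separately from each other.

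Nor does the loss fall on the main hypothesis. Dual against single blockade is available within every patient, and group II compares the two drugs by crossover.

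Finally, the largest gains in step 4 require both the raw-value reading and the within-patient reading of the SDs, at total SDs the protocol does not give. They should not be quoted as the size of the problem.

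One possible counter-argument fails. Group I is measured at baseline on habitual blockade with that morning's dose withheld, unlike later visits. Those conditions apply equally to both randomised arms, so baseline PWV remains a valid covariate.

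**Conclusion.** The point holds in conditional form and is one to consider. The only test section 5.14 names for PWV is an unpaired t-test with no baseline term in its power calculation. If it is carried into the group I comparison of the two drugs, a baseline-adjusted model has higher power than either the raw or the change-score version in every case computed here.

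The size depends on what the t-test would be applied to and what the SDs represent, neither of which the protocol states. For brachial PWV the gain is moderate at correlations of 0.5 or more against raw values, and small to moderate against changes. For aortic PWV it is negligible on the SDs at face value, and at most about 5 points against changes. All adjusted figures rest on assumed correlations or assumed total SDs.

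**What to change.** Add a sentence to section 5.14 saying that between-patient PWV comparisons will use a linear model of on-treatment PWV on randomised drug and Measurement I PWV, with group (I or II) as a factor when the two groups are pooled at the end of period 1. State also that the t-test served only for the power calculation.

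A mixed model over Measurements II to IV, with a patient effect, baseline PWV, group, period and treatment, is a separate option. It brings in the group II crossover and the dual-therapy period, so it is a different analysis from the period-1 model and not an equivalent one. The protocol should say which is primary.

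The cost is one or two degrees of freedom for the linear model. No new measurements or patients are needed.

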**7. Ethical considerations**
7.1 PROJECT IMPACT AND BENEFITS

The project will not have any consequences for the treatment of the individual patient. The intention is, that the project will lead to greater insight into the treatment of patients with chronic renal disease with drugs that block the renin-angiotensin system. This eventually allow for better intervention that may improve morbidity and mortality for patients with chronic nephropathy. Furthermore, the project contributes to an increased knowledge of applanationtonometry and its possibilities.

7.2 PROJECT RISKS AND DISADVANTAGES

1. Time consume
2. Discomfort of bloodsampling
3. Cr-EDTA clearance and thus ionized radiation

4. Adverse events associated with treatment

Removal of the maximum of 30 ml. of blood poses no risk.

The amount of ionizing radiation by a Cr-EDTA clearance is 0.01 mSv, and corresponds to one day of background radiation or radiation emitted by a conventional X-ray of an arm.

Applanationtonometry is noninvasive and poses no safety risk to the patient.

Adverse effects of ACE-I and AIIA are usually mild and transient.
When treated with ACE-I the following adverse effects can be seen: dry irritative cough, symptoms from the gastrointestinal tract such as nausea and diarrhea, and headache, fatigue, muscle cramps, and hyperkalemia. Angioneurotic edema, neutropenia and taste disorders are described. Hypotension. Renal impairment, which is usually reversible.
When treated with AIIA, the following adverse effects can be seen: dizziness, rarely orthostatic hypotension, rash, hyperkalemia and elevated liver enzymes, which normalize after discontinuation of therapy. Hypotension.
Contraindications for treatment of both drugs are renal artery stenosis or allergy towards the medicine.

It is ensured that fertile women are not pregnant when in the study in the form of a negative pregnancy test prior to enrollment in the trial. Moreover, it is a requirement for inclusion in the study that women of childbearing age use effective contraceptive methods. Safe contraception is due to the Medicines Agency one of the following methods: the pill, intrauterine device, depot gestagen injection, subdermal implantation, hormonal vaginal ring and transdermal patch. One of these methods must be used throughout the study period and for 1 week after the end of the study, which corresponds to 5 times the plasma half-life of the applied medication.

Recording and reporting of adverse events follow applicable laws. Referenced in the following text to the *Order of clinical trials of drugs in humans* defined types of side effect. Unexpected and serious suspected adverse reactions (Suspected Unexpected Serious Adverse Reactions, SUSAR) that are either fatal or life threatening will be reported to the Medicines Agency no later than 7 days after the sponsor-investigator has knowledge of them, and no later than 8 days after notification, the sponsor Investigators announce Medicines Agency all relevant information on follow-up. All other unexpected serious adverse reactions, will also be reported to the Medicines Agency no later than 15 days after the sponsor-investigator has knowledge of these. Serious, suspected adverse reactions (Serious adverse reaction, SAR) will be reported annually to the Medicines Authority. Serious adverse events and serious adverse events (Serious Adverse Events, SAEs) will be reported annually to the Scientific Ethical Committee. Adverse events and side effects will appear in the final report to the Medicines Authority of the study results.

If intolerable adverse effects, the participant will be withdrawn from the trial. The patient will then return to his usual medications and follow-up in the department of Nephrology, as long as required.

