• At the first day of the study the patient meets fasting from midnight and without smoking, but with permission to drink water. Alcohol should not be taken for 24 hours before study start. The patient waits to take his medication until after the study. For patients with diabetes, however, a light breakfast is consumed at home and the usual medications for diabetes, all medicines taken after the study. Investigations commenced approx. at. 9:00 after blood sampling and then 15 min. rest in supine position. The studies are carried out in a quiet room with ambient temperature 20-22 degrees. A total of 2 measurements are carried out by the same investigator.
After the measurement the patient's habitual ACE-I or AIIA therapy is discontinued and patients are randomized to a scenario with either Enalapril in the first and second periods (ACE-I group) or treatment with Candesartan in the first and second period (AIIA group). Common to both randomization groups is a common dual blockade with both Enalapril and Candesartan in the third period.
The ACE-I group is started in tablet Enalapril 5 mg daily and is given tablets until the next appointment. AIIA group is started in tablet Candesartan 4 mg daily and are given tablets until next appointment. For women of childbearing age, the drugs will only be supplied in case of a negative pregnancy test.

The patient must before start of treatment have had a Chromium-EDTA clearance performed as well as a 24 h urine collection, which is attempted planned for the day of measurement I.

Adjustment of medicine and clinical control Ia (after 2-3 weeks)
• Attendance in the morning for blood pressure measurement and blood sampling. Control of treatment. The AIIA-group is increased to a tablet of candesartan 8 mg daily and the ACE-I group is increased to a tablet Enalapril10 mg daily. Both groups were handed out tablets for next appointment.

Adjustment of medicine and clinical control Ib (after 5-6 weeks weeks)
• Attendance in the morning for blood pressure measurement and blood sampling. Control of treatment. The AIIA group increased to a tablet of candesartan 16 mg daily and the ACE-I group increased to a tablet Enalapril 20 mg daily. Both groups were handed out tablets for next appointment.

Measurement II (after approx. 8 weeks, 1^st^ period)

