• The patient meets fasting from midnight and without prior smoking, but with permission to drink water. Alcohol should not be taken for 24 hours before study start. A 24 hour urine collection is delivered for analysis. The patient is taking the study medication approx. 2 hours before meeting time. Any other medication is to be taken after the measurements on that day. For patients with diabetes however, a light breakfast and the usual medications for diabetes and the study medication are consumed at home, all other medication is to be taken after the measurement that day. Investigations are started approx. at. 9:00 after blood sampling and then 15 min. rest in the supine position. The measurements are carried out in a quiet room with ambient temperature 20-22 degrees. A total of 2 measurements are performed by the same investigator.
After the measurement, the patients in the ACE-I group continue taking a tablet of Enalapril 20 mg daily and patients in the AIIA group continue taking tablet candesartan 16 mg daily. They are handed out tablets to the next appointment.

Adjustment of medicine and clinical control IIa (after 10-11 weeks)
• Attendance in the morning for blood pressure measurement and blood sampling. Control of treatment. Patients in the ACE-I group continue on tablet Enalapril 20 mg daily. The AIIA group continues on tablet candesartan 16 mg daily. They are handed out tablets to next appointment.

Adjustment and control IIb (after 13-14 weeks)
• Attendance in the morning for blood pressure measurement and blood sampling. Control of treatment. Patients in the ACE-I group continue on tablet Enalapril 20 mg daily. The AIIA group continues on tablet candesartan 16 mg daily. They are handed out tablets to next appointment.

Measurement III (after about 16 weeks, second period)

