5.11 PARACLINICAL VARIABLE

The gained data is processed in the apparatus via a mathematical analysis to characterize the pulse wave and pulse wave velocity.
The following blood samples are taken at baseline and at all pulse wave measurements on all patients: b-hemoglobin, b-leukocytes, b-platelets, p-bilirubin, p-ALT, p-alkaline phosphatase, hsC-reactive protein, p-creatinine, p- urea, p-sodium, p-potassium, p-bicarbonate, glucose, p-albumin, p-cholesterol, p-triglyceride, p-HDL, p-LDL, p-urate, p-parathyroid hormone and p-homocysteine.

The following blood samples are taken at each clinical control: b-hemoglobin, p-creatinine, p-BUN, p-albumin, p-potassium and sodium.

*For blood samples:*At each blood sample a total of 30-40 ml of blood is taken. The blood will be analyzed immediately in connection with the measurement. An extra glass of blood will be taken in case of the need of reanalysis of samples.

*24 h urine collection*:
At baseline and at each measurement a 24 h urine collection ís delivered for analysis of urinary albumin and urinary sodium. The urine will be analyzed immediately in connection with the investigation. An extra glass of urine will be taken in case of the need of reanalysis of the sample. A pregnancy test in fertile women will be performed on a urine sample prior to entry into the study.

*Chromium-EDTA clearance*:
The estimated GFR <20 ml/min: 24h clearance with blood 5 and 24 hours after injection of 3.5 MBq of 51-Cr-EDTA.
The estimated GFR> 20 ml/min: blood sampling after 180, 200, 220 and 240 min. after injection of 3.5 MBq 51-CR-EDTA.

*Procedure regarding data at project completion*
All data will be stored for a maximum of 15 years, after which they will be destroyed. Data is stored in Nephrology Section B, KAS Herlev, and among the members of the project group. Data will only be available to the project group.

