Every 2^nd^ to 3^rd^ week the patient meets for blood pressure control and control of therapy. Blood sampling is carried out as described above. Study medication is adjusted.

*Chromium-EDTA clearance*There is a total of 2 study days for each patient on the department of clinical physiology, where the patient has a Cr-EDTA clearance performed. The days lies immediately before study start and after the termination of the study.
Intravenously injected 51 Cr-EDTA is excreted exclusively by glomerular filtration. Measurement of plasma concentration in one or more blood samples therefore allows calculation of the glomerular filtration rate.
At an estimated GFR <20 ml/min: 24 h clearance with blood sampling 5 and 24 hours after injection of 3.5 MBq of 51-Cr-EDTA.
At an estimated GFR> 20 ml/min: blood sampling after 180, 200, 220 and 240 min. after injection of 3.5 MBq 51-CR-EDTA.

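### The only pregnancy test in the visible text is at entry, so nothing scheduled would detect a pregnancy before the second-period supply or before dual blockade

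*Protocol*

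**What the plan says.** The protocol mentions pregnancy testing in these places, all concerning entry or the first supply:

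- Section 5.7 makes a negative test in fertile women an inclusion criterion.
- Section 5.11 fixes specimen and timing: "A pregnancy test in fertile women will be performed on a urine sample prior to entry into the study".
- Section 5.5, under Measurement I for patients with prior ACE-I/AIIA treatment (group I) and again for those without (group II), makes the first supply conditional: "For women of childbearing age, the drugs will only be supplied in case of a negative pregnancy test".
- Section 7.2 draws the conclusion: "It is ensured that fertile women are not pregnant when in the study in the form of a negative pregnancy test prior to enrollment".

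Section 7.2 also requires effective contraception: "One of these methods must be used throughout the study period and for 1 week after the end of the study". Section 5.9 lists pregnancy as a reason for withdrawal.

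On the later visits, section 5.11 says that the 24-hour urine at each measurement is "delivered for analysis of urinary albumin and urinary sodium". Section 5.12 introduces the later blood panel with "At the other measurements and clinical controls the following blood samples are taken for analysis" and lists haemoglobin, creatinine, urea, albumin, potassium and sodium. Section 5.11 gives a fuller panel for the measurement visits, also without a pregnancy test. The clinical controls are described as every second to third "week the patient meets for blood pressure control and control of therapy".

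**The concern.** A pre-enrolment test establishes status on one day. Section 7.2 presents it as securing non-pregnancy throughout participation, which it cannot do. Contraception lowers the chance of pregnancy but does not reveal its own failure. The withdrawal rule in 5.9 acts only once someone knows of the pregnancy.

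Two later supplies matter most. At Measurement II (about week 8), group II switches to the other drug, while group I stays on the same one (for example, "After the measurement, the patients in the ACE-I group continue taking a tablet of Enalapril 20 mg daily"). At Measurement III (about week 16), every patient starts the second drug on top of the first. A woman whose contraception has failed and who does not yet know it would receive these supplies without a check. That is the situation in which the protocol withholds drug at Measurement I.

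This is a participant-safety point. It does not touch the sample size, the endpoint or the analysis.

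**Working it through.** **Step 1: count the hand-outs (section 5.5).** Tablets are given out at Measurement I, controls Ia and Ib, Measurement II, controls IIa and IIb, Measurement III and the two period-three controls: 9 hand-outs. A pregnancy test is tied to 1 of them (Measurement I), leaving 9 − 1 = 8 without. Treatment lasts 3 × 8 = 24 weeks.

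**Step 2: consequence if a conception occurs.** The protocol gives no figure here, so this is an assumption-based range. Conception time c is uniform on 0 to 24 weeks. Exposure ends at the earliest of week 24, self-recognition at c + R, or a test at week 8 or 16 taken at least L weeks after c. R is none, 12 or 6 weeks. L, the time until a test turns positive, is 0, 2 or 3 weeks.

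Mean study-drug exposure after conception without later tests:

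- R none: 24/2 = 12.0 weeks.
- R = 12: (12 × 12 + 12 × 6)/24 = 9.0 weeks.
- R = 6: (18 × 6 + 6 × 3)/24 = 5.25 weeks.

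With tests at weeks 8 and 16 and R none:

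- L = 0: 8/2 = 4.0 weeks.
- L = 2: (6 × 5 + 8 × 6 + 10 × 5)/24 = 128/24 = 5.33 weeks.
- L = 3: (5 × 5.5 + 8 × 7 + 11 × 5.5)/24 = 144/24 = 6.0 weeks.

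For R = 12 these values are unchanged, because no exposure then exceeds 11 weeks.

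| Mean weeks of study drug after conception | No later test | L = 0 | L = 2 | L = 3 |
|---|---|---|---|---|
| Never recognised | 12.0 | 4.0 | 5.33 | 6.0 |
| Recognised after 12 weeks | 9.0 | 4.0 | 5.33 | 6.0 |
| Recognised after 6 weeks | 5.25 | 3.75 | 4.58 | 4.88 |

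**Step 3: share of conceptions in which dual blockade starts during pregnancy.** Without a later test, c must lie before week 16 and be unrecognised at week 16:

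- R none: 16/24 = 67%.
- R = 12: (16 − 4)/24 = 50%.
- R = 6: (16 − 10)/24 = 25%.

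With a test at Measurement III, only conceptions in the last L weeks are missed: L/24 = 0%, 8.3% or 12.5%.

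**Step 4: weeks of dual blockade.** This is the relevant measure for group I, whose patients already take one of the two drug classes.

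| Mean weeks of dual blockade | No later test | With tests (L = 0 / 2 / 3) | Saved |
|---|---|---|---|
| Never recognised | 6.67 | 1.33 / 2.0 / 2.33 | 5.33 / 4.67 / 4.33 |
| Recognised after 12 weeks | 4.0 | 1.33 / 2.0 / 2.33 | 2.67 / 2.0 / 1.67 |
| Recognised after 6 weeks | 2.0 | 1.25 / 1.67 / 1.81 | 0.75 / 0.33 / 0.19 |

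**Step 5: how often.** Expected conceptions are N × (1 − (1 − p)^(24/52)), where N is the number of fertile women and p the annual conception risk on contraception. The protocol gives neither; both are assumed.

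- N = 2, p = 0.1%: 0.0009.
- N = 6, p = 1%: 0.028.
- N = 12, p = 9%: 0.51.

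**The case against.** The strongest reply is that the absence cannot be proved. A visit-level test would normally appear in the flowcharts (Appendix Ia/Ib), the patient meeting schedule (Appendix IId) or the registration form for measurements and controls (Appendix IVb), and none is shown. This stands as a limit: those documents are not judged. But the visit descriptions in 5.5 are detailed, and 5.11 and 7.2 place the test before entry. If later tests exist, the body text still needs to say so.

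Second, an entry test, mandatory contraception and withdrawal for pregnancy form a coherent strategy, backed by frequent controls and round-the-clock access to a nephrology doctor (7.3). Such contact makes a never-recognised pregnancy unlikely, so those figures are an upper bound. With recognition after 6 weeks the saving is only 0.38 to 1.5 study-drug weeks. That is a fair reduction in size, but none of these contacts is a pregnancy check.

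Third, the event is rare. In the middle case of 0.028 conceptions, dual-blockade starts averted are 0.028 × 0.125 to 0.028 × 0.67, or about 0.003 to 0.019 per trial. This stands, and it means the case rests on low cost, not on frequency.

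Fourth, group I is 40 of the 60 patients (5.6). They already take an ACE-I or AIIA and return to usual medication on withdrawal (5.13), so fewer study-drug weeks need not mean less exposure to the class. Their clear gain is avoided dual blockade, and the documents do not state how much worse two drugs are than one in pregnancy. This stands too.

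Finally, an 8-week interval is a judgement. It is chosen because it coincides with the two main treatment decisions and with urine already delivered.

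**Conclusion.** The concern holds. On the visible text, testing ends at entry or first supply, eight further hand-outs follow without a test, and the assurance in 7.2 claims more than one baseline test can support.

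Conditional on a conception, tests at Measurements II and III would lower the share starting dual blockade while pregnant from 25–67% to 0–12.5%. Mean study-drug exposure would fall from 12.0 to 4.0–6.0 weeks at the upper bound, and from 5.25 to 3.75–4.88 weeks if the woman recognises the pregnancy after 6 weeks. Expected conceptions are about 0.001 to 0.5. All of this rests on assumed recognition times, test lag, number of fertile women and conception risk.

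The change should be made because it is cheap and lets the protocol's own withdrawal rule act before the two main treatment steps. Confidence is medium because the appendices are not shown.

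**What to change.** - In 5.5 and 5.11, repeat the urine pregnancy test in fertile women at Measurements II and III, using urine already delivered at those visits.
- Make the hand-outs at those two visits conditional on a negative result, as 5.5 already does at Measurement I.
- Reword 7.2 to say that non-pregnancy is confirmed at entry, supported by mandatory contraception, and rechecked at Measurements II and III.
- A test at Measurement IV, when study drug stops, is optional documentation only.
- If the flowcharts or forms already contain these tests, only 5.5, 5.11 and 7.2 need aligning.

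The cost is two urine tests per fertile woman (2 × 2 = 4 to 2 × 12 = 24 tests for an assumed 2 to 12 women) and one case report form line. No visit or invasive procedure is added, and sample size and primary analysis do not change. Limits remain: gaps of about 8 weeks persist, a conception in the 2 to 3 weeks before a test may be missed, and a group I woman withdrawn for pregnancy may still return to her habitual ACE-I or AIIA under 5.13.
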